#### Factors that influence implementation

The Consolidated Framework for Implementation Research (CFIR) is a theoretical framework for the collection and analysis of potential factors within the Leben QD II study that influence implementation
[43]. The CFIR consolidates constructs of published implementation theories, using the question “what works where and why across multiple contexts”
[43]. The constructs are sorted into 5 domains: “intervention characteristics,” “outer setting,” “inner setting,” “characteristics of the individuals involved,” and the “process of implementation.” Damschroder LJ, 2009
[43] Different types of data will be collected to explore facilitators of and barriers to DCM implementation, using the CFIR framework.

To explore all CFIR domains, semi-structured interviews will be performed with head nurses (T0, T2) and staff nurses (T1) from each participating nursing home involved in the implementation process. The process documents will provide information about the implementation process within each setting.

Feedback meetings on the DCM process and case conferences in the second comparison group will be performed once per intervention cycle to assess team interaction and the “inner setting.” A German version of the SYMLOG-Rating Scale by Schneider/Orlik
[44] and field notes will be used to document these interactions. Finally, data from the questionnaire on organizational characteristics (‘inner setting’) and the staff questionnaire (T0/T2) (‘characteristics of individuals’) will also be used to evaluate the implementation process.

## Data analysis

### Effect analysis

Resident and staff outcomes from the intervention and comparison groups will be compared using descriptive and advanced statistical methods at T0, T1 and T2. A multilevel modeling approach will be conducted to evaluate differences between the intervention group and both control arms regarding the development of primary and all secondary outcomes during the study period. This approach will be used to account for the hierarchical structure of the data (i.e. residents with dementia/staff members are nested within institutions and measurement points). To evaluate the effect of assignment the intention to treat principle (ITT) will be applied. The results of ITT will be compared to a per protocol analysis to assess the effect of intervention adherence (degree of implementation). In all analytical steps, the effect estimates will be adjusted for baseline differences and differences in the influencing factors at all measurement points. We will use subgroup analysis to compare the intervention group to comparison group 2. Residents who drop out of the study or are lost to follow up will be described. A statistician who is blinded to group assignment will perform the statistical analyses.

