[22,23]. The DCM observational instrument is embedded in the DCM method, which consists of 6 fixed components: 1) briefing and preparation of care staff and leadership, 2) DCM observation, 3) DCM data analysis and report-writing, 4) feedback of results to care staff and leadership, 5) action-planning by care staff based on the DCM results and 6) realization of the action plan
[24].

The engagement of care staff to take an active and accountable role is part of the DCM process. This process is repeated to create an ongoing development of PCC. The successful use of DCM to advance PCC has been reported in several studies
[7,16,23,25,26]. Positive effects included improved well-being of residents, higher quality staff interaction
[23] and lower rates of agitation
[7]. Additionally, DCM use might help staff to adopt a holistic approach when attending to the needs of residents
[16]. The effects of DCM are highly dependent on the implementation process, which is influenced by multiple factors
[24]. Moreover, the implementation of DCM has to be carefully considered because of relatively high costs in time, staff education, and external consulting for example,
[7,8] compared to the implementation of other Qol tools.

PCC and DCM have been equally well known in Germany for several years. The first trainings in DCM were carried out in 1998, and interest has been continuously growing. DCM is used in care homes, small-scale living arrangements and day care settings. Since 2009, the increasing interest in using DCM and other Qol measurements in German nursing homes has partly been emerged from the assessment of residents´ quality of life through care audits of the medical advisory service of the statutory health insurance
[27]. Up to now there has been no study about the effectiveness of DCM on residents with dementia and nursing staff in Germany. There are some evaluation reports about DCM projects
[28,29] with hypotheses generating results for Germany. These reports suggest that DCM enhances PCC and that a successful implementation depends on several factors.

Results indicate that for a successful use of DCM staff members need to have a good interaction quality within the team, they should have higher job satisfaction and a small rate of staff turnover. If teams have these characteristics, residents wellbeing seems to increase
[28].

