## Methods/design

### Design

To measure the effects of DCM a quasi-experimental design is being used, with 3 measurement points (Figure 
1). 9 nursing home units will be assigned to either the DCM intervention group or 1 of 2 comparison groups. The care provider will be responsible for the assignment of a unit to 1 of the 3 groups. The DCM method will be implemented in the 3 units assigned to the intervention group. The first comparison group will consist of 3 nursing units that have at least 3 years of experience in the use of the DCM method. The 3 units in the second comparison group will receive a control intervention based on the use of the dementia-specific Qol-measurement QUALIDEM. Quantitative methods will be used to study the effects and cost-effectiveness. A broad explorative mixed-methods approach will be used for the process evaluation.

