#### Degree of implementation

Semi-structured interviews with head nurses (T2) and staff nurses (T1) involved in the implementation process in each nursing home will be used to gather information on the degree of implementation following the concept of implementation fidelity
[42]. Likewise, single items of the staff questionnaire (T2) will assess implementation fidelity by asking in which way staff members are involved in the intervention and how they judge the implementation process.

Furthermore a random sample of 3 resident records per participating institution (T0, T1, T2) will be collected and reviewed for indicators of successful implementation of PCC. An increase in written statements about psychosocial needs of an individual resident will reflect implementation of PCC.

Environmental assessment using the DMA (T0, T2) will also serve to assess changes during implementation and the degree of implementation. Finally, documents will be collected to reconstruct the implementation process within each institution to see if the implementation process has been conducted as intended. Such documents might include implementation concepts, information sheets/flyers, reports on relevant specific meetings and project-related emails.

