## Discussion

This quasi-experimental study will provide important information on the effects of DCM on residents and staff, implementation of DCM and cost-effectiveness of DCM in German nursing homes. The findings will be an important basis for the design of a subsequent randomized controlled trial.

DCM is a specific intervention with fixed elements and a defined implementation process. It is known that the implementation of DCM in an institution has a strong influence on residents and staff members, the health care team as a whole and the climate and management of an organization. The effects of DCM are strongly influenced by the interaction between the different levels of the organization and organizational readiness
[43]. For example, an interested team with motivated change-agents but with an adverse management might not be able to implement DCM to a degree that will result in an improvement of the Qol of the residents. Thus, in addition to the measurement of the intervention’s effects, a major focus of this study is the evaluation of the degree of implementation and the identification of main barriers to and facilitators of implementation. These findings will help nursing home decision-makers and managers decide whether to use DCM, and the results will help to design an adequate implementation process for DCM and other psychosocial interventions.

The following information will be generated and used in the design of a subsequent RCT on effectiveness of DCM in German nursing homes:

a. The appropriateness of the primary and secondary outcomes and important variables and their measurement.

b. Identification of characteristics of nursing homes and units that have a strong influence on the successful implementation of DCM. This information could be used to define inclusion criteria for nursing homes and units and to ensure maximum organizational readiness.

c. Information about helpful adaptations for the DCM implementation process.

d. Information about the treatment and control differences, attrition rate, standard deviation and the interclass correlation coefficient that is needed for a sample size calculation in a subsequent randomized controlled trial.

e. The subgroup analysis of control residents will give some indications about the spillover-effect of PCC on other residents who were not included in the DCM-cycle.

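### The gap between the ITT and per-protocol results is to be read as the effect of adherence, but degree of implementation arises after allocation, mainly at institution level, so the contrast is likely to remain confounded

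*Protocol article*

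**What the plan says.** The Effect analysis section uses ITT for the effect of assignment and then adds: "The results of ITT will be compared to a per protocol analysis to assess the effect of intervention adherence (degree of implementation". The next sentence plans adjustment, in every step, for baseline differences and for influencing factors at all measurement points.

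The design has nine units, one per nursing home, in three groups of three:

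- Intervention group: "The DCM method will be implemented in the 3 units assigned to the intervention group".
- Comparison group 1: "The first comparison group will consist of 3 nursing units that have at least 3 years of experience".
- Comparison group 2: "The 3 units in the second comparison group will receive a control intervention".

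Allocation is not random: "The care provider will be responsible for the assignment of a unit to 1 of the 3 groups".

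The section on degree of implementation lists head-nurse and staff-nurse interviews, staff questionnaire items, three resident records per institution, the environmental assessment and process documents. The documents serve this purpose: "documents will be collected to reconstruct the implementation process within each institution to see if the implementation process has been conducted as intended". The Process analysis section then brings these sources together institution by institution.

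On what governs implementation, the Background reports from earlier DCM projects that successful use needs good interaction within the team, job satisfaction and low turnover. It adds: "If teams have these characteristics, residents wellbeing seems to increase". The Discussion says that the effects of DCM depend on organizational readiness and gives the example that "an interested team with motivated change-agents but with an adverse management might not be able to implement DCM to a degree" sufficient to improve residents' quality of life.

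**The concern.** A difference between an ITT and a per-protocol estimate measures the effect of adherence only if the adherent and non-adherent are otherwise comparable. Here adherence is a result that develops during the study in each home. The article names the conditions that produce it: team, turnover, management and readiness. Job satisfaction is named as one of these conditions and is also a secondary staff outcome. A home that implements well may therefore also be one where outcomes would have developed better anyway.

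If so, a per-protocol result that looks better than the ITT result could arise with no adherence effect at all. The Discussion intends the study to help managers decide whether to use DCM and how to implement it. A gap reported as the effect of good implementation would bear on both decisions.

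**Working it through.** The article states no sample size, power, alpha, SD or intraclass correlation, so there is no planned figure to reproduce. The check has two parts.

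**1. Can the planned adjustment remove the confounding?**

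- Between-unit information: 9 units − 3 groups = 6 degrees of freedom. Few unit-level covariates can be fitted.
- Form of the factors: Table 1 lists interviews and process documents among the influencing factors. These do not readily become model covariates.
- Overlap: in Table 1 the same interviews and process documents also supply the degree of implementation. Adjusting for one while selecting on the other does not separate them cleanly.
- Timing: factors measured at T1 and T2 may already have been changed by the intervention. Adjusting for them can remove part of the effect or introduce new bias.

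The adjustment may reduce the confounding, but it cannot be relied on to remove it.

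**2. How large could the distortion be if whole units leave the per-protocol set?**

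Inputs: 3 units per group (Design section). Assumptions: a two-sided 5% level, unit outcomes approximately normal, true DCM and adherence effects both zero, no adjustment, and a correlation r between a unit's implementation and its outcome. The article gives no r, so a range is shown.

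*Shift in the group mean.* The expected largest of 3 standard normal values is 0.8463 and the expected smallest is −0.8463. The three expectations sum to zero, so the mean of the upper two is 0.8463/2 = 0.423. When units are ranked by implementation, the expected outcome shift is r times these values:

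| r | Drop the worst of 3: 0.423 × r | Keep only the best: 0.846 × r |
|---|---|---|
| 0.3 | 0.13 | 0.25 |
| 0.5 | 0.21 | 0.42 |
| 0.7 | 0.30 | 0.59 |
| 0.9 | 0.38 | 0.76 |

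The unit is the between-unit SD of the outcome. A simulation of 400,000 sets of units agrees (for r = 0.5: 0.211 and 0.423), with the ITT contrast averaging zero. The whole shift therefore appears as a gap between per-protocol and ITT.

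*Precision.* The 95% half-width for a v b units, in SDs of unit means, is t(0.975, a + b − 2) × √(1/a + 1/b):

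| Units | df | Calculation | Half-width | Ratio to 3 v 3 |
|---|---|---|---|---|
| 3 v 3 | 4 | 2.776 × 0.816 | 2.27 | 1.00 |
| 2 v 3 | 3 | 3.182 × 0.913 | 2.91 | 1.28 |
| 2 v 2 | 2 | 4.303 × 1.000 | 4.30 | 1.90 |
| 1 v 3 | 2 | 4.303 × 1.155 | 4.97 | 2.19 |

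**The case against.** **The plan adjusts for the influencing factors.** It does, and those factors include staffing, turnover and team interaction. It would be wrong to call the planned contrast unadjusted or certainly confounded. What stands is that adjustment is weak here, for the reasons in part 1 of the check.

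**Nothing says that whole units are dropped.** Correct. A reader might infer it from the institution-level measurement, but the article fixes neither an adherence threshold nor a level of exclusion. The Discussion mentions residents outside the DCM cycle, which leaves room for a resident-level definition. The missing definition may sit in an analysis plan not shown and is no finding. The unit-level figures are therefore conditional.

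**The text describes readiness as acting on the effect of DCM or through implementation, not as a separate cause of quality of life.** This is a fair reading of the Discussion. The Background sentence on well-being is hedged and comes from reports on DCM projects. The documents support only that these factors may also relate to the outcomes.

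**The illustration uses an unadjusted outcome, while the plan models adjusted development over time.** This also stands. The formula applies to adjusted change if r is read as the correlation with that change. Adjustment that worked well would lower r, and with it the shift.

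**The shift lies well inside the intervals.** True: 0.13 to 0.38 against half-widths of 2.27 and 2.91. The figures do not show that a false significant result is likely. They show that a gap can arise on average without any adherence effect.

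**The inclusion criteria of the later trial do not rest on this contrast.** A reader might infer that they do. The Discussion bases them on home and unit characteristics that influence implementation, which come mainly from the process evaluation.

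**Conclusion.** The stated purpose of the per-protocol comparison is unsound as worded. Degree of implementation is a post-allocation characteristic, measured mainly per institution and tied by the article to organizational conditions that may also relate to outcomes. The contrast is likely to remain confounded despite the planned adjustment.

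The size is illustrative only. It rests on an assumed r of 0.3 to 0.9, no true effect, no adjustment, and exclusion by unit. On those terms, losing the worst-implementing of three units shifts the group mean by 0.13 to 0.38 between-unit SDs, and moving from 3 v 3 to 2 v 3 widens a 95% interval by about 28%.

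The documents do not support the stronger reading that the plan will drop whole units and will produce a false adherence effect of known size. Nor is the as-assigned contrast a clean benchmark: the care provider chose the groups, and the article acknowledges the lack of randomization. The per-protocol step adds a second selection to the first.

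**What to change.** In the Effect analysis section:

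1. Delete the clause that gives the per-protocol comparison the purpose of assessing the effect of adherence.
2. State that conclusions on the effect of assignment rest on the as-assigned analysis with all nine units kept, subject to the acknowledged lack of randomization.
3. If a per-protocol result is reported, label it exploratory and non-causal.
4. Within the per-institution comparison already planned under Process analysis, show each unit's degree of implementation beside its baseline-adjusted change and its T0 readiness measures (for example turnover and T0 job satisfaction). Label the display hypothesis-generating.

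The cost is a change of wording and one table built from data that the study already plans to collect. The downside is that the nominal per-protocol test of adherence is given up.

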**Cost effectiveness**		
**Domain**	**Instrument/source**	**Type of variable**
Resource use	Nursing home administration system	Cost outcome

The data collection times will be oriented with the DCM cycles in the intervention group and will take place before starting the implementation (DCM training) (T0, months 1 to 3) and no more than 2 months after the first (T1, month 9–11) and the third (T2, months 21–23) DCM-cycle. The data collection times for the process evaluation and the implementation process will correspond with T0 to T2 (Figure 
1). Cost data for the economic evaluation will be extracted from the nursing home administrative system at the end of the intervention period.

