#### Institution-level measures

Potential institutional influences will be assessed in relation to the organizational characteristics of the respective unit and the “dementia-friendliness” of the environment. To accomplish this, 2 instruments were developed during the preparation phase of the Leben-QD II study. The Dementia-Institution-Questionnaire (DIQ), which evaluates organizational characteristics, is divided into 2 domains. The first domain consists of 4 items and evaluates whole institution structure and financing. The second domain focuses on the nursing unit and is divided into the resident-specific factors (3 items), structure (1 item) and staffing, including staff turnover (5 items). The DIQ will be completed every 3 months by the study coordinator of the corresponding institution.

To assess “dementia-friendliness” the Dementia Milieu Assessment (DMA) will be used, which consists of 29 items. The DMA is a standardized observation instrument. The factors are divided into an environmental domain (21 items) and a psychosocial domain (8 items). Each item has yes or no dichotomous response options. Scores range from 0 to 21 for the environmental domain and from 0 to 8 for the psychosocial domain. Higher scores indicate a more dementia-friendly environment. The DMA is used during a 2-hour period of observation from 3–5 pm in each facility. The observation is carried out in the public space only, and resident rooms are not included. A scientific staff member with experience in dementia-specific observations is responsible for completing the DMA. Both instruments will be tested for their psychometric properties during the study.

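### The effect model adjusts for undefined influencing factors at T1 and T2; where DCM can change such a factor, the model no longer estimates the effect of assignment

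*Protocol article*

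**What the plan says.** The protocol article's Effect analysis section plans multilevel models for the primary and all secondary outcomes. It names the target: "To evaluate the effect of assignment the intention to treat principle (ITT) will be applied". A per-protocol analysis is planned alongside to address adherence. The covariate rule then opens "In all analytical steps, the effect estimates will be adjusted", and its content is that "the effect estimates will be adjusted for baseline differences and differences in the influencing factors at all measurement points".

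T0 precedes the DCM training. The other two points fall "no more than 2 months after the first (T1, month 9–11) and the third (T2, months 21–23) DCM-cycle" (Measures/data collection, text after Table 1).

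The Effect analysis section does not define the influencing factors. Table 1 uses the label in its implementation block, for interviews, single items of the staff questionnaire, the DIQ, SYMLOG and process documents. Resident and staff covariates such as FAST, PSMS, medication and BelaDem burden are called control variables instead. On timing: "The DIQ will be completed every 3 months by the study coordinator of the corresponding institution". The meetings rated with SYMLOG "will be performed once per intervention cycle to assess team interaction".

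**The concern.** An effect of assignment includes whatever the intervention does by changing the team, the staffing and the organisation. A covariate that is measured after the intervention starts, and that responds to it, holds part of that effect constant. It can also bring in bias through unmeasured causes that it shares with the outcome.

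The rule is stated outright, so an analysis plan that followed it would carry the problem forward. The estimates answer research questions 1 and 2. They are to inform the sample size of a later randomised trial (Discussion, item d). If the cost-effectiveness ratios use them as denominators, an effect that is halved doubles the ratio, since 1/0.5 = 2.

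**Working it through.** The protocol gives no effect size, standard deviation or mediated share, so there is no planned figure to reproduce. The check compares sections, followed by an illustration of the mechanism.

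**1. Can DCM change these factors?** The Discussion says that implementing DCM strongly affects staff, the care team, and the climate and management of the organisation. The DIQ's 5 staffing items include turnover, and the questionnaire is repeated during the intervention.

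**2. Can these factors affect the outcomes?** The Background reports that residents' well-being seems to rise where teams interact well, are more satisfied and have low turnover. Together with step 1, this makes a path from DCM through staffing and team to the outcome plausible on the protocol's own account.

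**3. Staff outcomes.** Under Measures for caregivers, single items cover dementia-specific knowledge and emotional job satisfaction. Job satisfaction on the COPSOQ scale is a secondary outcome. If Table 1's label is taken literally, a follow-up outcome could be adjusted for something close to itself.

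**4. If control variables were meant.** FAST and demographic data are unlikely to respond to DCM. Medication could respond. BelaDem burden is rated in relation to residents' challenging behaviours, so it lies close to the NPI-NH outcome.

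**5. Effect analysis against Process analysis.** The Process analysis section assigns interviews to content analysis, process documents to a database, staff-questionnaire and structural data to descriptive statistics, and SYMLOG to field diagrams. It keeps effect and process data with different researchers until a final merging step. The Effect analysis section adjusts for influencing factors in every step. Both cannot hold for the same set of factors.

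**6. Illustration (all values assumed, none from the protocol).** Let a be the effect of group on the later factor, b the effect of the factor on the outcome, and c the remaining direct effect. Then total = c + a·b, and a model that adjusts for the factor returns c. Take total = 0.40 and a = 0.5.

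| Share through the factor | a·b | Adjusted, c | Adjusted, with a shared unmeasured cause |
|---|---|---|---|
| 0% | 0.00 | 0.40 | 0.36 |
| 25% | 0.10 | 0.30 | 0.26 |
| 50% | 0.20 | 0.20 | 0.16 |
| 75% | 0.30 | 0.10 | 0.06 |

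The last column gives the unmeasured cause a coefficient of 0.3 on both factor and outcome, with unit residual variance. The shift is a × 0.3²/(1 + 0.3²) = 0.5 × 0.09/1.09 = 0.041. A simulation of 400,000 individually randomised records without clustering gave 0.397, 0.293, 0.203 and 0.100 for the third column, and 0.353, 0.261, 0.157 and 0.054 for the fourth. Estimates without the later factor stayed between 0.394 and 0.404.

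Two further cases set the limits. If the group does not affect the factor (a = 0), nothing is lost (0.400). If the indirect path has the opposite sign (a·b = −0.10, c = 0.50), adjustment raises the estimate from 0.40 to 0.50.

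**The case against.** The strongest defence is that this is a non-randomised study: the care provider assigns units, and participants lost to follow-up are replaced. Case mix can therefore shift at T1 and T2, and adjusting for current severity and dependency is a reasonable way to control confounding. This stands for factors that DCM is unlikely to change. It does not justify adjusting an effect of assignment for later staffing, team or staff-response variables.

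It is also fair to say that the list of adjusted factors is uncertain. Interviews and posters are not natural regression covariates. SYMLOG is tied to intervention meetings and goes to field diagrams, and individual characteristics from the staff questionnaire are used at T0 and T2 only. Of the instruments labelled as influencing factors, the DIQ is the most credible covariate. Some DIQ content, such as institutional structure and financing, is unlikely to move with DCM. This narrows the point but does not remove it, because nothing limits the rule to such content.

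A reader might infer four stronger claims that the document does not support:

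- **A known loss of effect.** Any figure in Qol-AD points would only restate an assumed mediated share.
- **An overfitted unit-level model.** Setting the 13 DIQ items against 9 units presumes that every item enters separately, which is stated nowhere.
- **No unaffected comparison at all.** Descriptive comparisons at T0, T1 and T2 are also planned, although they are not described as adjusted for baseline differences.
- **A breach of intention to treat as such.** That principle fixes analysis by assigned group, not the covariate set. The conflict is with the stated target, the effect of assignment.

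**Conclusion.** The point holds in conditional form. The adjustment rule is stated for every effect estimate and reaches past baseline, its key term is undefined, and it cannot be squared with the Process analysis section as written. Where a DCM-responsive factor enters at T1 or T2, the group coefficient is no longer the total effect of assignment. Candidates are DIQ staffing and turnover, single staff items or, on the other reading, medication and BelaDem burden.

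Attenuation is the most likely result, because the protocol expects DCM to work partly through team and organisation. That rests on two assumptions: that DCM moves these factors, and that their effect on the outcome has the same sign as the direct effect. Size and direction cannot be computed from the document. For factors that DCM does not change, this loss of effect does not arise.

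**What to change.** Replace the covariate sentence in the Effect analysis section with a rule of this kind:

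- In the primary intention-to-treat model, adjust only for pre-specified covariates measured before the intervention (T0).
- For residents who join later as replacements, use entry values of case-mix factors that DCM is unlikely to change, for example age, gender, FAST and PSMS. A literal T0-only rule would leave these residents without covariates.
- Move T1 and T2 values of DCM-responsive factors (DIQ staffing and turnover, single staff items, medication, BelaDem burden) to the process evaluation, or to a separately labelled exploratory mediation or sensitivity analysis.
- Define the influencing factors by name, and align the Effect analysis section with the Process analysis section on where each is used.

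One limit should be stated in the text: comparison group 1 has used DCM since 2009, so its T0 values are not free of exposure.

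No new instruments are needed. The cost is a short rewrite and somewhat less control of case-mix or institutional changes after entry; the sensitivity analysis can show how much that matters.
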